## 1. Title

Double-blind, Multi-center randomized, prospective confirmatory clinical study to evaluate the efficacy and safety of MegaShield using for anti-adhesion after total thyroidectomy

## 6. Purpose and background

### 6.1 Purpose of clinical trial

It is widely known that postoperative administration of anti-adhesion has an effect of preventing adhesion on surgical sites and surrounding tissues. In this clinical trial, the anti-adhesion effect and safety are compared and evaluated by applying either MegaShield or Guardix-SG after thyroidectomy to patients who have undergone total thyroidectomy in order to evaluate the postoperative anti-adhesion effect of MegaShield.

### 6.2 Background of clinical trial

Adhesion refers to a phenomenon in which surrounding organs or tissues that must be separated from each other adhere to each other due to excessive generation of fibrous tissue or leakage and coagulation of blood during the healing process of wounds due to inflammation, cut, friction, surgery, etc. Adhesion can generally occur after any type of surgery. Since excessive adhesion or unintended adhesion with other organs or tissues causes organ dysfunction, in some cases, Adhesiolysis is required. Adhesion can also be a life-threatening factor. There are many different types of sequelae that can be caused by such adhesion. [1-4] According to statistical data in the United States, it is known that the main symptoms of postoperative adhesion are 49 to 74% in ileus, 15 to 20% in infertility, 20 to 50 in chronic pelvic inflammatory disease [5-6], and 19% in enterobrosia during follow-up surgery. [7]

General prevention of adhesion formation includes: 1) minimizing adhesion during surgery; 2) suppressing adhesion by treating with medication, such as anti-inflammatory drugs, anticoagulants, fibrinolytic agents and antibiotics, in the pathophysiological process necessary for the adhesion formation and inflammatory reactions based on the adhesion mechanism; and 3) preventing adhesion by using anti-adhesions after surgery to cover wound area or block contact with surrounding tissues [8-11]. However, these methods have limitations that can reduce the formation of adhesion but cannot eliminate it, requiring a lot of attention.

Since the prevention of adhesion after surgery is a very important factor in reducing complications, meticulous surgical methods and anti-adhesion are used to prevent adhesion, but there is currently no unique product that has excellent anti-adhesion effect. [6,8]

In the case of the existing liquid type anti-adhesion, it is often difficult to apply accurately to the wound due to severe flowing down when applied in the body, or it breaks down too early to prevent adhesion. In the case of film or membrane type, when applied to internal organs, it has poor adhesiveness, and foreign body reactions appear. In addition, the folding and adhering properties of the film make it difficult to apply to minimally invasive surgery or laparoscope, require sutures, and cause adhesion to the suture area. Since gel types melt and discharge before the wound is healed and there is insufficient time to stay in the wound tissues, it does not properly show anti-adhesion effects and non-biomaterial exhibits foreign body reaction in vivo [8].

Anti-adhesion must be safe and effective first. It must also remain while the damaged tissue is healed, preventing adhesion between tissues adjacent to the wound and the fibrous tissues, and then be naturally decomposed, absorbed and removed [12]. And to ensure anti-adhesion function, it must have excellent adhesion so that it can be continuously adhered to the wound caused by surgery, and it must be an injectable type suitable for minimally invasive surgery or laparoscope.

Recently, anti-adhesion products with thermo-sensitive polymers have been released to meet these four conditions. The main ingredients of the composition are Poloxamer 407 (Pluronic F-127) and Poloxamer 188 (Pluronic F-68), and typical examples include a mixture of thermo-sensitive polymer and sodium alginate, and a mixture of thermo-sensitive polymer, gelatin and chitosan (Korea Patent Publication No. 10-1452041 and No. 10-1330652).

Poloxamer has a unique property of having a sol-to-gel transition temperature due to its self-adhesive above a certain concentration, and it is biocompatible and less toxic [13]. Sodium alginate is a natural polysaccharide extracted from brown algae, consisting of  $\beta$ -D-mannuronate and  $\alpha$ -L-glucuronate. It forms a gel by cross-linking with calcium ions, has no immunological activity, and is not digested by animal cells.

These thermo-sensitive compositions are convenient to use because they exist in a liquid state at room temperature and in a viscous gel state near body temperature, however they still require longer-term monitoring for anti-adhesion, in vivo persistence, adhesiveness, etc. [12,14]

Based on this background, the sponsor of this clinical trial strove to develop an anti-adhesion composition with these properties: thermo-sensitivity, which enables sol-to-gel phase transition; user-friendly convenience; excellent biocompatibility; in vivo persistence; adhesiveness to tissue; biodegradability; and ultimately excellent anti-adhesion effect. As a result, it developed MegaShield, a human tissue-derived thermo-sensitive anti-adhesion, which is a mixture of collagen-based granular acellular dermal matrix, hyaluronic acid and thermo-sensitive polymer. MegaShield has the following advantages. It is convenient to use by its phase transition from a sol state to a gel state by body temperature so that it can be stably applied in tissues. It can also effectively inhibit the formation of adhesion because it has excellent biocompatibility, in vivo persistence, adhesiveness to tissues, and biodegradability. Therefore, MegaShield is a next-generation anti-adhesion product that has both convenience of use and anti-adhesion functionality. It has been reported that the

acellular allogenic dermal matrix, one of the raw materials of MegaShield, has the effect of anti-adhesion in many surgical treatments, and studies have shown that transplanting acellular allogenic dermal matrix after thyroidectomy has an anti-adhesion effect [15]. In addition, an animal test on rats demonstrated that MegaShield has sufficient functionality as an anti-adhesion. This clinical trial is intended to verify the efficacy and safety of MegaShield.

## **7. Overview of investigational product (purpose of use, target disease, or indication)**

**Purpose of use :** MegaShield is a product developed to be used for preventing adhesion after total thyroidectomy, which removes all thyroid tissues visible to the naked eye [16]. MegaShield is a mixed solution with a composition of water-soluble polymers capable of sol-to-gel transition and with high biocompatibility. It exists in a sol (liquid) state at room temperature and becomes viscous gel at body temperature after being applied in the human body. This acts as a physical barrier, which has effect on preventing adhesion from forming by providing a lubricating surface between adjacent tissues or organs while tissue wounds heal.

**Target:** Patients with total thyroidectomy

## **8. Inclusion criteria and exclusion criteria for those who are subject to investigational product or are included in the control group and participate in the clinical trial (hereinafter, "subjects"), the number of them and these basis**

### **8.1 Inclusion criteria**

Subjects who meet all of the following criteria shall participate in the clinical trial:

- (1) a patient who gives written informed consent spontaneously;
- (2) a patient who is between 20 and 70 years of age;
- (3) a patient who can participate the clinical trial during the entire study period;
- (4) a patient who is required total thyroidectomy due to thyroid disease;
- (5) a patient who are scheduled to undergo thyroidectomy for the first time related to thyroid disease;
- (6) a patient with no liver dysfunction, anemia or renal inadequacy in preoperative testing; and
- (7) a patient who agreed to contraception while participating in the clinical trial after application of investigational product.

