| Investigational Device           | 
 
· Experimental : MegaShield: A transparent or milky gel-type liquid manufactured by mixing acellular dermal matrix powder, cross-linked hyaluronic acid and thermo-sensitive polymer(poloxamer)
 
· Comparator : Guardix-SG: A product consisting of poloxamer and sodium alginate
 
                                                                                                                                                                                                                                                                                                                                                                                                                                                                                                                                                        |
| Inclusion and Exclusion Criteria | 
<Inclusion Criteria>
 
Subjects who meet all of the following criteria shall participate in the clinical trial:
 
 
1) a patient who gives written informed consent spontaneously;
 
2) a patient who is between 20 and 70 years of age;
 
3) a patient who can participate the clinical trial during the entire study period;
 
4) a patient who is required total thyroidectomy due to thyroid disease;
 
5) a patient who are scheduled to undergo thyroidectomy for the first time related to thyroid disease;
 
6) a patient with no liver dysfunction, anemia or renal inadequacy in preoperative testing; and
 
7) a patient who agreed to contraception while participating in the clinical trial after application of investigational device.
 
 
<Exclusion Criteria>
 |

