### **8.2. Exclusion criteria**

Subjects who fall under any of the following criteria shall be excluded from the clinical trial:

- (1) a pregnant or breast-feeding female patient; or a female who plans to become pregnant within 1 month after applying the investigational product;
- (2) a patient with serious liver or kidney disease;
- (3) a patient with lymphatic or hemostatic disorders; or a patient taking an anticoagulant;
- (4) a patient who receives an oral or a parenteral hypoglycemic agent for diabetes;
- (5) a patient immunosuppressed; or a patient with autoimmune diseases;
- (6) a patient with serious systemic disease;
- (7) a patient scheduled for accompanied follow-up surgery;
- (8) a patient undergoing chemotherapy for a cancer other than thyroid cancer;
- (9) a patient who is treated by another anti-adhesion; or
- (10) a patient deemed inappropriate for this study by the investigator (including non-cooperative, etc.).

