## 10.4 Study procedure

### 【Schedule of Clinical Study】

| Item                                         | Screening | Application and Evaluation |         |          |
|----------------------------------------------|-----------|----------------------------|---------|----------|
| Visit                                        | Visit 1   | Visit 2                    | Visit 3 | Visit 4  |
| Day                                          | -30~0     | Day 0                      | Day 7±3 | Day 42±7 |
| Written consent                              | ●         |                            |         |          |
| Inclusion/exclusion criteria                 | ●         |                            |         |          |
| Demographic survey/physical examination      | ●         |                            |         |          |
| Vital signs test                             | ●         |                            |         | ●        |
| Medical/administering history  | ●         |                            |         |          |
| Subjects enrollment                          |           | ●                          |         |          |
| Surgery and applying investigational product |           | ●                          |         |          |
| Esophagography                               |           |                            |         | ●        |
| Evaluating adhesion scores                   | ●         |                            | ●       | ●        |
| Urine β-HCG testing (for fertile women)      | ●         |                            |         | ●        |
| Hematological test                           | ●         |                            | ●       | ●        |
| Serum biochemical test                       | ●         |                            | ●       | ●        |
| Urinalysis                                   | ●         |                            | ●       | ●        |
| Collecting concomitant drug    | ●         | ●                          | ●       | ●        |
| Collecting adverse event       |           | ● (After surgery)          | ●       | ●        |

(1) Collect medical history within 5 years before participating in the clinical trial.

(2) Collect information on drugs that have been administered within 4 weeks of the screening visit or are currently being administered.

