## **11.1. Observation and clinical testing items**

### 1) Visit 1 : Screening (Day -30~0)

Subjects who have agreed to participate in this clinical trial should be screened to ensure that they are eligible to participate in the study.

- Receive informed consent
- Review inclusion/exclusion criteria
- Demographic survey/physical examination : Date of birth, gender, weight, height, etc.
- Vital signs test : Blood pressure, pulse rate
- Medical/administering history : Diabetes mellitus, hypertension, stroke, ischemic heart disease, malignant tumor, acute infection, allergy, and whether taken bisphosphonate, etc.
- Evaluate adhesion scores
- Urine  $\beta$ -HCG testing (only for women with childbearing age)
- Hematological test : RBC, Hemoglobin, Hematocrit, Platelet, WBCs, Neutrophil, Lymphocyte, Monocyte, Eosinophil, Basophil, Blood coagulating time (PT/APTT)
- Serum biochemical test : sodium, Potassium, Chloride, Creatinine, BUN, ALT, AST,ALP, Total Bilirubin, Albumin, Total Protein, Total Cholesterol, Glucose
- Urinalysis : pH, Specific gravity, WBC, Protein, Bilirubin, Glucose, Urobilinogen, Ketone, Nitrite, Blood
- Collect concomitant drugs

### 2) Visit 2 : Day 0

- Perform a surgery and apply an investigational product
- Enroll subjects
- Collect concomitant drugs
- Collect adverse events : After surgery

### 3) Visit 3 : Day 7 $\pm$ 3

- Evaluate adhesion scores
- Hematological test : RBC, Hemoglobin, Hematocrit, Platelet, WBCs, Neutrophil, Lymphocyte, Monocyte, Eosinophil, Basophil, Blood coagulating time (PT/APTT)
- Serum biochemical test : sodium, Potassium, Chloride, Creatinine, BUN, ALT, AST,ALP, Total Bilirubin, Albumin, Total Protein, Total Cholesterol, Glucose
- Urinalysis : pH, Specific gravity, WBC, Protein, Bilirubin, Glucose, Urobilinogen, Ketone, Nitrite,

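### Contraception is required only after the product is applied, so up to 30 days between the screening pregnancy test and surgery are uncovered

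*Protocol*

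**What the plan says.** **Contraception.** Section 8.1, inclusion (7), requires "a patient who agreed to contraception while participating in the clinical trial after application of investigational product". The summary's inclusion list repeats it, with one word changed: "a patient who agreed to contraception while participating in the clinical trial after application of investigational device".

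**Pregnancy exclusion.** Section 8.2, exclusion (1), bars "a pregnant or breast-feeding female patient" and also "a female who plans to become pregnant within 1 month after applying the investigational product". The first clause has no date limit. The second counts only from application.

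**Testing.** The schedule row "Urine β-HCG testing (for fertile women") is marked at Visit 1 and Visit 4 only, and the visit lists in section 11.1 agree. Visit 1 is headed "Visit 1 : Screening (Day -30~0") and Visit 4 is Day 42±7.

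**Eligibility review.** Section 11.1 lists "Review inclusion/exclusion criteria" under Visit 1, and the schedule marks that row at Visit 1 only. The Visit 2 list begins "Perform a surgery and apply an investigational product" and adds enrollment, concomitant drugs and adverse events after surgery. It names no pregnancy test and no second look at eligibility.

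**History.** Section 11.2.2 asks about pregnancy status and plans before the trial starts.

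**Product precautions.** Section 12.3.3 advises against using the comparator in pregnancy, and advises avoiding pregnancy until the first menstrual cycle after use has ended. Section 12.2.3, for the test product, names pregnant women in its heading, but its text deals only with allergy and reduced immunity.

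**The concern.** The protocol intends that no pregnant woman receives either product. What matters for that aim is whether she is pregnant on Day 0, so the controls need to cover the days leading up to Day 0. Inclusion (7) covers only the days after it, and so does the planned-pregnancy clause of exclusion (1). The one control that looks at the earlier period is the Visit 1 test, which may be 30 days old by the time of surgery.

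What is at stake is participant safety: a product applied during an early pregnancy that nobody has recognised. For the comparator, the protocol itself advises against such use. For the test product, no section states a fetal hazard, and none is claimed here. The thyroidectomy is needed whether or not the patient joins the trial, so only the exposure to the product is added by the trial. The primary analysis is unaffected.

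**Working it through.** No sample-size, power or error-rate figure bears on this point. The check compares the dates and counts days.

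**Inputs**

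| Item | Timing | Source |
|---|---|---|
| Screening visit, with β-HCG test | Day -30 to Day 0 | 11.1, schedule |
| Application of product | Day 0 | 11.1, schedule |
| Next β-HCG test (Visit 4) | Day 42±7, that is Day 35 to Day 49 | 11.1, schedule |
| Contraception required | From application, while in the trial | 8.1(7), summary |
| Eligibility review | Visit 1 only | 11.1, schedule |

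**Step 1: days between the screening test and application.** Shortest: 0 − 0 = 0 days. Longest: 0 − (−30) = 30 days. Inclusion (7) requires no contraception in this interval, and no further test is scheduled in it.

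**Step 2: days from exposure to the next test.** 42 − 7 = 35 and 42 + 7 = 49, so 35 to 49 days.

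**Step 3: days from a conception in the gap to the next test.** Conception on Day 0 and a test on Day 35: 35 − 0 = 35 days. Conception on Day -30 and a test on Day 49: 49 − (−30) = 79 days. These figures show when the schedule would be expected to find the pregnancy. They do not measure harm.

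**Step 4: what else could catch it before application.**
- Exclusion (1) has no date limit, so a pregnancy known on Day 0 still excludes. It cannot act on an unknown one.
- The question on pregnancy status and plan in 11.2.2 can bring out an intention to conceive. It cannot reveal an unrecognised conception that happens later.
- Section 10.4 has the criteria checked before codes are assigned, after the hematology, biochemistry and urinalysis results are seen. It does not call for a repeat β-HCG test.

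None of these would reveal an unrecognised conception between the Visit 1 test and Day 0.

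**Step 5: effect of moving the start of contraception to screening.** Now: Day 0 to Visit 4, 35 to 49 days. After the change: Visit 1 to Visit 4, from 35 + 0 = 35 to 49 + 30 = 79 days. The added commitment is 0 to 30 days, and the interval without required contraception becomes 0 days.

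**The case against.** The strongest reply is that nothing here contradicts anything else. Avoiding pregnancy after use is exactly what section 12.3.3 advises for the comparator, and exclusion (1) separately bars pregnancy before use. On that reading, contraception from consent is only a stricter preference. The real gap would then be the timing of the test, and rewording inclusion (7) detects nothing.

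This stands in part. The rewording lowers the chance of a pregnancy on Day 0 but does not find one, and it does not help with a conception too recent for the Visit 1 test to show. Still, the start date in inclusion (7) is an explicit rule, and it leaves open the very days that decide whether exclusion (1) is met at application.

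Other points limit the size of the concern without removing it:
- Thirty days is a maximum, and a patient screened close to surgery has almost no gap.
- The earlier a conception falls in the window, the more likely it is to be noticed by Day 0.
- Enrollment takes place on Day 0 and remains conditional on the criteria; a known pregnancy excludes and a stated plan can surface at screening. What remains is mainly an unplanned and unrecognised conception.
- A hospital may test before anesthesia, but this protocol does not require it.
- The consent form (section 16) is not shown and may already ask for contraception from consent. That would soften the practical effect, but the criterion itself would still start at application.

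**Conclusion.** The concern holds as a minor safety point. As written, inclusion (7) leaves 0 to 30 days between the screening test and application with no contraception requirement and no repeat test, and the next scheduled test comes 35 to 49 days after exposure.

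The conclusion rests on the text of sections 8.1, 8.2, 10.4, 11.1 and 11.2.2, the schedule and the summary. The number of fertile women among the 140 subjects aged 20 to 70, and the usual interval from screening to surgery, are not given. No frequency can therefore be put on it, and the number of women affected may be very small or none. There is no consequence for the treatment estimate, the margin, the power or the sample size.

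**What to change.** In section 8.1(7) and the matching line of the summary, require contraception from the screening β-HCG test (consent) through Visit 4. The cost is up to 30 more days of commitment before surgery and one change of wording in two places. No visit or test is added.

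As an option for the sponsor, add a urine β-HCG test and an eligibility re-check at Visit 2 before application. This would bring the longest interval from the last test to application down from 30 days to about 0, at a cost of one urine test per fertile woman at an existing visit. It may still miss a very recent conception, so it complements the wording change and does not replace it.

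The sponsor should check whether the consent form already asks for contraception from consent or needs the same wording.

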### **8.2. Exclusion criteria**

Subjects who fall under any of the following criteria shall be excluded from the clinical trial:

- (1) a pregnant or breast-feeding female patient; or a female who plans to become pregnant within 1 month after applying the investigational product;
- (2) a patient with serious liver or kidney disease;
- (3) a patient with lymphatic or hemostatic disorders; or a patient taking an anticoagulant;
- (4) a patient who receives an oral or a parenteral hypoglycemic agent for diabetes;
- (5) a patient immunosuppressed; or a patient with autoimmune diseases;
- (6) a patient with serious systemic disease;
- (7) a patient scheduled for accompanied follow-up surgery;
- (8) a patient undergoing chemotherapy for a cancer other than thyroid cancer;
- (9) a patient who is treated by another anti-adhesion; or
- (10) a patient deemed inappropriate for this study by the investigator (including non-cooperative, etc.).

